#### ***Other variables***

The primary independent variable is the GP’s assigned study group (intervention or control group).

Patient variables: age, sex, new statin prescription picked up from a pharmacy, cardiovascular risk (calculated using the REGICOR formula and recorded in ECAP), cholesterol (total, LDL and HDL), systolic and diastolic blood pressure, smoking habit, treatment group from the catalog of statins (Anatomic, Therapeutic, Chemical [ATC] code), and diagnosed cardiovascular disease, diabetes mellitus, or hypertension, according to International Classification of Diseases (ICD-10 codes), listed below:

– Myocardial infarction: I21 and subtypes, I22 and subtypes, I23 and subtypes, I25.2

– Ictus: I60 and subtypes, I62 and subtypes, I63 and subtypes I64

– Peripheral artery disease: I73, I73.8, I73.9

– Tobacco use: F17 and subtypes F17.1 – F17.9

– Diabetes Mellitus: E11 and subtypes, E12 and subtypes, E13 and subtypes, E14 and subtypes

– Arterial hypertension: I10, I15, I15.1, I15.2, I15.8, I15.9.

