### Study population

Twelve PCC are excluded because their current participation in a different intervention could invalidate the results of this study. The research team will identify all patients aged 35 to 74 years who received a new prescription for cholesterol-lowering drugs from the remaining 271 PCC during the study period (October 1, 2011-September 30, 2013), as recorded in the electronic medical records system, known as ECAP. Exclusion criteria are any history of cardiovascular disease (ischemic heart disease, cerebrovascular accident, or peripheral artery disease) recorded in ECAP and patients for whom pharmacy records showed receipt of a cholesterol-lowering prescription drug during the 12 months preceding their inclusion in the study.

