### Intervention design

Based on the list of patients with inclusion and exclusion criteria, the research team will analyze the adequacy of new prescriptions for cholesterol-lowering drugs, based on the recommendations contained in ICS clinical practice guidelines on cholesterol and coronary risk [26]. The flow chart for this analysis is included as Additional file 1.

All GPs assigned to the intervention group will receive informational feedback about the adequacy of cholesterol-lowering drugs prescribed for their patients. Feedback is provided as part of the ECAP system capabilities. The preparation and dissemination of intervention-related feedback will be monthly, beginning in the second year of the study (October 1, 2012-September 30, 2013). This information, available to the GPs at their convenience, will be presented in two distinct and complementary formats and updated throughout 12 consecutive months:

1. Asynchronous information (patient not present)

a) Quantitative information about the percentage of the GP’s assigned patients who have started primary cardiovascular prevention therapy with cholesterol-lowering drugs and that is considered correctly indicated according to the criteria established in the corresponding ICS clinical practice guidelines [26].

b) List of names of patients who have started primary cardiovascular prevention therapy with cholesterol-lowering drugs but do not meet the guidelines criteria.

2. Real-time information (patient present when information is presented to GP).

3. In each GP’s daily schedule, an alert symbol will indicate appointments with patients who have started statins therapy for primary cardiovascular prevention without meeting the established indications criteria. In addition, a message will be included in the ECAP system of clinical advisories. This screen, used during the patient visit, shows all active clinical advisories and alerts for that specific patient. This may include EQA information, medication safety considerations, notice of availability of test results, etc.

The GPs assigned to the control group will not receive the project’s ECAP feedback. The study algorithm is diagrammed in Additional file 2.

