### Outcomes

New treatment with cholesterol-lowering drugs is defined as a prescription given to a patient who has not collected any such prescription from a pharmacy during the 12 months preceding study inclusion, according to national health system records.

Primary prevention is considered the absence of cardiovascular disease (ischemic heart disease, cerebrovascular accident, peripheral artery disease).

The ICS clinical practice guidelines on cholesterol and coronary risk are applied to determine prescription adequacy when cholesterol-lowering drugs are prescribed for primary prevention [26]. To operationalize the algorithm, adequate treatment is defined as meeting one or both of the following criteria:

A. At least 10% cardiovascular risk, according to REGICOR 10-year risk calculated within 12 months of treatment initiation. The REGICOR risk function has been calibrated and adapted to local incidence and distribution of risk factors in Catalonia [27]. It stratifies cardiovascular risk into 4 classifications: low (<5%), moderate (5%–9.9%), high (10%-14.9%), and very high (>15%). The ICS clinical practice guidelines recommend the use of REGICOR tables to calculate coronary risk and consider individuals with at least 10% risk of a 10-year coronary event to be candidates for more intensive interventions, which may include cholesterol-lowering drugs. Additional file 3 contains the REGICOR risk tables, adapted from the Framingham risk calculation.

B. At least 240 mg/dl LDL cholesterol recorded during the 12 months preceding treatment initiation.

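### The ICD-10 list for cardiovascular disease is narrower than the exclusion it would have to serve: infarction codes only for the heart, and no I61 for stroke

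*Protocol article*

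**What the plan says.** In the protocol article, Study population excludes patients with "any history of cardiovascular disease (ischemic heart disease, cerebrovascular accident, or peripheral artery disease) recorded in ECAP". Outcomes repeats the three disease groups: "Primary prevention is considered the absence of cardiovascular disease (ischemic heart disease, cerebrovascular accident, peripheral artery disease". Neither section gives codes.

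Codes appear once, under Other variables, where the patient variables include "diagnosed cardiovascular disease, diabetes mellitus, or hypertension, according to International Classification of Diseases (ICD-10 codes), listed below". The cardiovascular part of the list has three lines:

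- The line for the heart is "Myocardial infarction: I21 and subtypes, I22 and subtypes, I23 and subtypes, I25.2".
- The line for stroke is "Ictus: I60 and subtypes, I62 and subtypes, I63 and subtypes I64".
- The line for the peripheral arteries gives three codes, I73 itself together with I73.8 and I73.9.

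Data collection and follow-up, and again the Discussion, say that discharge records from public hospitals will supplement the diagnoses. No separate code set is stated for them.

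Under Outcomes, a new prescription is adequate if it meets at least one of two criteria: REGICOR 10-year risk of at least 10%, or LDL cholesterol of at least 240 mg/dl. Under Intervention design, GPs in the intervention arm receive, among other things, a "List of names of patients who have started primary cardiovascular prevention therapy with cholesterol-lowering drugs but do not meet the guidelines criteria". They also see an alert at the patient's visit.

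**The concern.** The three cardiovascular lines of the list match the three excluded disease groups one for one, so the list reads as the working definition of the exclusion. Two of the lines are narrower than the group they stand for.

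This matters because neither adequacy criterion recognises established cardiovascular disease. Removing such patients at eligibility is the only step that keeps them from being judged by primary-prevention criteria. The Background says that the indication for treatment is not in doubt in secondary prevention. A patient with excluded disease who slips through can nevertheless be classed as inadequately treated, and stopping that patient's drug would count towards an increase in RETIRA, which the plan defines as improvement.

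**Working it through.** No arithmetic applies and the plan states no figure on this point. The check sets the sections side by side and then follows one patient through the rules.

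**Step 1: compare the groups with the codes.**

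| Excluded group (Study population, Outcomes) | Label in Other variables | Codes listed | Not listed |
|---|---|---|---|
| Ischemic heart disease | Myocardial infarction | I21, I22, I23, I25.2 | I20, I24, rest of I25 |
| Cerebrovascular accident | Ictus | I60, I62, I63, I64 | I61 |
| Peripheral artery disease | Peripheral artery disease | I73, I73.8, I73.9 | not at issue here |

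The label of the first line already shows the narrowing: infarction is one part of ischemic heart disease. In the second line, four of the five categories from I60 to I64 are present.

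**Step 2: look for another definition.** There is none in the article. The sections on discharge data name a source, not a code set.

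**Step 3: follow a patient.** Take someone aged 35 to 74 whose only cardiovascular record is an unlisted code, for example within I20 or I61, and who starts a cholesterol-lowering drug.

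1. If the list is the exclusion filter, the ECAP record does not exclude this patient.
2. The 12-month dispensing rule does not exclude the patient either, since the treatment is new.
3. Discharge data exclude the patient only if there was an admission to a public hospital and the codes searched there are wider than the list.
4. If the patient is still in, with REGICOR risk below 10% and LDL below 240 mg/dl, the prescription is classed as inadequate.
5. A start in the year before the intervention puts the patient among those assessed for RETIRA. A start in the 12 months of follow-up puts the patient in EVITA. The cost enters COST.
6. In the intervention arm the patient is named to the GP.

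**Step 4: size.** The number affected is the number of new starts with only unlisted codes, times the share not recovered from discharge data, times the share meeting neither adequacy criterion. The documents give none of these three quantities. Sample size mentions about 60,000 new statin treatments a year, but nothing on diagnosis codes. No estimate follows.

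**Step 5: direction.** Both arms use the same list, so the eligibility error is not expected to unbalance them at baseline. It puts the wrong patients into the outcomes of both arms, and into the feedback of one.

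**The case against.** The strongest reply is that the link from list to exclusion is inferred. The codes stand among descriptive patient variables. The eligibility text is broader and does not refer to them. The flow chart and the study algorithm are in additional files that are not shown. The extraction may have used a fuller list, and the missing I61 may be a misprint, since that line also lacks a separator before I64. This stands as a limit on the claim, which is therefore conditional. It does not remove the inconsistency: the article does fix a definition of diagnosed cardiovascular disease, it is the only one given, and it does not match the exclusion.

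Discharge data are a real safeguard, and no section confines them to the listed codes. They still miss patients never admitted to a public hospital. Study population ties the exclusion to disease recorded in ECAP, and the article does not say whether discharge data fed the alerts.

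Four stronger readings are tempting and not supported:

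- A reader might infer that the whole list covers only infarction. That is true of the heart line alone; stroke and peripheral artery codes are present.
- A reader might infer that patients were harmed. The feedback is informational and GPs consult it when they choose. Patients already dispensed such a drug in the previous 12 months are excluded whatever their codes. Harm would need several further steps that the documents do not show.
- A reader might put a number on the misclassified patients. Any such number would rest on shares that appear nowhere in the documents.
- A reader might set the misclassified share against the 1% difference named under Sample size. The two are not alike: one is a share of patients present in both arms, the other a difference between arms. If a share c responds with effect d' and the rest with d, the observed effect is (1 − c)d + c·d'. For illustration only, assume c = 5%, d = 10 points and d' = 0. The result is 0.95 × 10 = 9.5 points, a shift of 0.5 points towards no effect. With d = 1 point it is 0.95.

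**Conclusion.** The concern holds in conditional form. The exclusion and the only published code list disagree: the heart line has infarction codes alone, and the stroke line omits I61. If the list served as the exclusion filter, some patients with excluded disease remain as primary prevention, and those meeting neither adequacy criterion are misclassified in RETIRA or EVITA and COST. In the intervention arm they also appear in the feedback.

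This rests on two assumptions that the documents neither confirm nor rule out: that the list defined the exclusion, and that discharge data do not close the gap completely. The size is unknown and the error applies to both arms. It deserves correction because it reaches both primary outcomes and is cheap to remove, not because a large bias has been shown.

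**What to change.** Reconcile Study population, Outcomes and Other variables into one ICD-10 list that covers all ischemic heart disease and all cerebrovascular accident codes, and state that it defines the exclusion. Apply it to both ECAP and hospital discharge data, for eligibility and for analysis. Re-derive RETIRA, EVITA and COST with it. Report how many patients flagged to GPs had excluded disease under the reconciled list; this supplies the size that the documents cannot give.

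The same list should govern the alerts if that is still possible. It may not be: the feedback period ran from October 2012 to September 2013 and registration is dated November 28, 2013. In that case the correction is confined to the analysis and the count.

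The cost is a repeat of the extraction and a slightly smaller sample. If a wider list was in fact used, correcting the published list and saying so is enough.

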#### ***General practitioner variables***

– EQR: SIDIAP has developed this synthetic index showing the quality standard of each GP’s data recording in the ECAP system.

– EQPF: This ICS synthetic indicator reflects the quality (adequacy) of drug prescription for each GP.

– EQA: This ICS synthetic indicator reflects the overall quality of care provided by each GP, based on established ICS standards.

– Use of the intervention: SISAP provides a monthly summary of the number of time each GP accesses the information provided in ECAP.

– Teaching responsibilities: This variable reflects whether or not the GP works with a resident physician.

The patient and GP variables analyzed also allow a description of the use of cholesterol-lowering drugs for primary prevention and the associated factors that are relevant to the secondary objectives.

### Data collection and follow-up

Most of the study variables will be obtained from the population-based SIDIAP database (*Sistema d’Informació pel Desenvolupament d’Investigació en Atenció Primària*) [28], which is similar to other European databases such as Clinical Practice Research Database (CPRD), Quality database for ethical research (QRESEARCH), Out-Patient Pharmacy Database (PHARMO), or The Health Improvement Network (THIN). The SIDIAP database contains anonymized data from 5.8 million individual patients in the ICS electronic medical records system and from complementary sources that provide valid, reliable information for research about primary care. This database is representative of Catalonia as a whole (http://www.sidiap.org) and includes the following information:

1. ECAP data on sociodemographic variables, primary care visits, diagnoses (ICD-10 codes), clinical variables, prescriptions, immunizations, and background. ECAP implementation began in 1998 and has been used in routine practice since 2005 in all PCC managed by ICS.

2. Pharmacy records:

Pharmacy records: Information on medication dispensed in community pharmacies since 2005, including the associated cost.

3. Laboratory tests: Results are available for all tests since 2006.

Finally, to complete the identification of patients with a history of cardiovascular disease, hospital discharge data are available for all public hospitals in Catalonia (Minimum Basic DataSet).

### Sample size

The preliminary study conducted by the research team showed the availability of a sample size of approximately 60,000 new statin treatments prescribed each year. Assuming 90% strength, 5% alpha error, a 1:1 ratio of control to intervention participants, corrected by the cluster design and assuming 10% loss to follow-up, our study could detect a difference of 1% (according to the medical criteria applied by the experts on the research team) at a 90% confidence interval. Even with this strength level, a clinically relevant difference of 10% can be established.

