### Statistical analysis

Initially, descriptive analysis will be completed for all study variables: mean (standard deviation) for continuous variables with a normal distribution, median (interquartile ranges) in the case of non-normal distribution and the frequency (percentage) of categorical variables. Differences between the intervention and control groups will be assessed using the χ2 or Fisher exact test for categorical variables and Student *t* for continuous variables with normal distribution, or nonparametric Mann–Whitney U test, as appropriate. Differences between means, medians, or ratios at the beginning and end of the two-year follow-up period (pre- and post-intervention) will be compared using the McNemar test, Student *t* for paired tests, or Wilcoxon test, as appropriate.

The percent change with respect to baseline value is used as a measure of the pre- and post-intervention change in categorical variables, calculated as the final percentage minus the initial percentage × 100.

The intervention effect after one year of follow-up will be evaluated using the decrease in the EVITA variable and increase in the RETIRA variable. To assess the effect of the intervention model, a multilevel logistic regression analysis will be performed, considering intervention vs control group as the independent variable. The analysis will be adjusted for potential predictive independent variables and, for those considered clinically relevant, for baseline values.

To determine the economic impact of new prescriptions of cholesterol-lowering drugs in primary prevention prescribed during the study period, a descriptive analysis of costs and resource use will be completed for each study group and the groups will be compared (discount rate: 3%). The incremental cost-effectiveness ratio will be calculated as the difference between the cost average for the 2 study groups, divided by the difference between the effects for both groups. Acceptance curves will be calculated to determine the cost-effectiveness of the intervention compared to usual practice.

Significance will be established at the 5% level. All analysis will be done using Stata/SE, version 10.1 (StataCorp).

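### The stated 1% detectable difference is not supported by one year of about 60,000 new treatments unless the outcome is rare or near-universal and clustering is very small

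*Protocol article*

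**What the plan says.** The Sample size section starts from a "sample size of approximately 60,000 new statin treatments prescribed each year". It sets the error rates ("Assuming 90% strength, 5% alpha error"), 1:1 allocation, a correction for the cluster design and 10% loss to follow-up. It concludes that the study "could detect a difference of 1% (according to the medical criteria applied by the experts on the research team) at a 90% confidence interval", and adds that "a clinically relevant difference of 10% can be established". It gives no control rate, ICC, design effect or sidedness, and does not say whether the figure refers to RETIRA or EVITA.

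Four other places matter:

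- Study population and Randomization: 271 primary care centers remain, and the center is the unit of randomization.
- Primary outcomes: EVITA concerns inadequate new treatments started in the 12-month follow-up. RETIRA concerns treatments started in the year before the intervention that were judged inadequate and later stopped.
- Statistical analysis: "Significance will be established at the 5% level".
- Discussion: the authors say that a large share of patients is treated outside the guidelines, without giving a number.

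**The concern.** A detectable difference of 1 percentage point between two proportions needs a very large sample unless the proportion is close to 0 or 1. Sixty thousand treatments sounds ample, but neither primary variable can draw on more than one year of starts, RETIRA uses only a subset of its year, and all patients sit in 271 randomized clusters of about 200 each. The printed 1% is said to hold after the cluster correction, yet over a wide range of control rates the sample falls short before any correction is made.

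What is at stake is interpretation. A reader who trusts the figure could take a non-significant result as good evidence against effects of 1 point or more, although power for such an effect may be far below 90%. The 90% confidence interval attached to the figure is a smaller conflict: it does not match a two-sided 5% test.

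**Working it through.** **Inputs from the protocol.** 60,000 starts a year; 10% loss, so 60,000 × 0.90 = 54,000 evaluable, or 27,000 per arm; 271 centers, so m = 54,000 / 271 = 199.3 per center; power 90%; alpha 5%.

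**Assumptions.** Two-sided alpha; the 1% read as 1 percentage point; all 60,000 starts eligible; EVITA analysed as a proportion of year-2 starts; control rate p and ICC varied, because the article gives neither.

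**Formula.** Detectable difference = (1.960 + 1.2816) × √(2p(1−p) × DE / n per arm), with DE = 1 + (m − 1) × ICC.

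**1. Trying to reproduce the 1%.** With p and ICC both absent, it can be neither reproduced nor refuted from the stated inputs alone. The useful question is for which values it could hold.

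**2. One year, no clustering (DE = 1, n = 27,000).**

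- p = 20%: 3.2416 × √(0.32 / 27,000) = 1.12 points
- p = 30%: 3.2416 × √(0.42 / 27,000) = 1.28 points
- p = 50%: 3.2416 × √(0.50 / 27,000) = 1.39 points

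Solving with the variance of each arm's own rate, 1 point at 90% power is out of reach for control rates from about 15% to 84%. Ignoring the 10% loss (60,000) gives about 17% to 82%. A one-sided 5% test, which would fit a 90% interval, gives about 19% to 80%.

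**3. Where 1 point is attainable.** For a 1-point increase, the largest ICC that still allows it is about 0.002 at a 10% rate, 0.007 at 5% and 0.02 at 2%. For a decrease from 5%, the limit is about 0.01. Pooling both years (108,000, DE = 1) gives 0.99 points at a 50% rate, but neither primary variable uses both years.

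**4. EVITA with clustering (assumed ICC 0.01 to 0.05).** DE = 1 + 198.3 × 0.01 = 2.98, and 1 + 198.3 × 0.05 = 10.9.

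| Control rate | ICC 0 | ICC 0.01 | ICC 0.05 |
|---|---|---|---|
| 20% | 1.12 | 1.93 | 3.69 |
| 30% | 1.28 | 2.21 | 4.22 |
| 50% | 1.39 | 2.41 | 4.61 |

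At a 30% rate, power for a true 1-point difference is 71%, 31% and 12% at ICC 0, 0.01 and 0.05. At 50% it is 64%, 27% and 10%.

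**5. RETIRA.** Assume that half of the year-1 starts are inadequate: 27,000 evaluable, 13,500 per arm, m = 99.6, DE = 1.99 at ICC 0.01 and 5.93 at ICC 0.05.

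- Withdrawal rate 10%: 1.18 points unclustered; 1.67 to 2.88 with clustering (about 1.6 to 3.1 when solved separately for a decrease and an increase).
- Withdrawal rate 50%: 1.97 points unclustered; 2.78 to 4.81 with clustering.

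**6. The 10% difference, read as 10 points.** With 54,000 evaluable, power is at least 99.9% at ICC 0.05 to 0.10, and about 96% at ICC 0.20 with a 50% rate.

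**The case against.** The strongest reply is that the article says the figure was corrected for clustering and simply does not print the control rate and ICC. A journal article may leave those to the full protocol, so their absence is no fault in itself, and for some values the 1% is correct. This stands, and it limits the conclusion: a flat statement that the design fails to deliver 1 point goes further than the document allows. It does not rescue the figure for EVITA, because the authors' own description of widespread inappropriate treatment makes a rare outcome unlikely. The remaining route is a rate above about 84% with almost no clustering. The description is not a number, so that route is not excluded.

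Four stronger readings are tempting and are not supported:

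- That the design detects 2 to 5 points. This is one assumed scenario. Over rates of 5% to 50% and ICC 0.005 to 0.10, the range is about 0.9 to 6.4 points for EVITA.
- That the 1% arises only by pooling both years. Step 3 shows other routes within one year.
- That RETIRA is the less well powered outcome. That needs equal base rates, and the two variables measure different things. RETIRA at a 10% rate (1.7 to 2.9 points) does better than EVITA at 50% (2.4 to 4.6) for the same ICCs.
- That 1% and 10% are contradictory targets. One is a detectable difference, the other a clinically relevant one.

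The 90% interval may be loose wording for 90% power, or may reflect a one-sided 5% test, since the hypotheses are directional. The significance level itself is stated consistently as 5%.

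**Conclusion.** The concern holds in conditional form. For any control rate between about 15% and 84%, one year of 54,000 evaluable treatments does not give 90% power for 1 point with a two-sided 5% test, even with no clustering, and randomizing 271 centers makes it worse. The conditional result rests on stated inputs plus a two-sided test and an absolute reading of the 1%; a one-sided test changes the range little. The sizes with clustering rest on the assumed rates, ICCs and, for RETIRA, the assumed inadequate share.

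A reader might infer that the trial is underpowered. The documents do not support that: the clinically relevant 10% remains well powered. The error lies in the stated detectable difference, and its severity is moderate.

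**What to change.** Replace the 1% statement with a minimum detectable difference for each primary outcome on the denominator that follows from its definition: year-2 starts for EVITA, and year-1 starts judged inadequate for RETIRA. Use 271 centers, 10% loss, 90% power, two-sided 5% alpha, and the control rate and ICC from the preliminary data. Print those two inputs and report whatever values result; the ranges above are illustrations and should not be adopted as the answer. Say whether the difference is absolute or relative. Delete "at a 90% confidence interval" or correct it to agree with the 5% significance level. Keep 10% as the clinically relevant difference.

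The cost is one reworded paragraph and a short calculation on data that the team already holds. No extra patients or centers are needed. The only drawback is that the stated figure will probably be less favourable.
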